## Abstract

**Background:**

The rising prevalence of diabetes, particularly in low- and middle-income countries, highlights an urgent need for innovative approaches to prevention. India faces a growing burden of type 2 diabetes (T2D), placing considerable strain on affected individuals and healthcare systems. This study aims to evaluate the effectiveness of a digital intervention designed to prevent T2D in individuals with pre-diabetes in India.

**Methods:**

A total of 3,240 individuals with pre-diabetes will be recruited across urban and rural settings in Tamil Nadu and Delhi. Participants will be cluster randomised to either the digital intervention group or the control group (usual standard of care). Clusters will comprise of wards in urban areas and villages in rural areas. Initial screening will be conducted using the Indian Diabetes Risk Score (IDRS) ≥ 30 and/or a random capillary blood glucose level ≥ 110 mg/dL. Final recruitment into the study will be based on capillary oral glucose tolerance testing (OGTT) and/or HbA1c levels. The primary outcome is incidence of T2D at 24 months, and secondary outcomes are cardiometabolic events, lifestyle and behavioural factors, and cost effectiveness of digital interventions. The study is registered with the Central Trials Registry of India (CTRI/2022/02/040650).

**Discussion:**

This protocol paper details the comprehensive study design aimed at evaluating the effectiveness of a digital intervention to prevent T2D in India. If effective, the study will provide important insights into the use of technology in resource-constrained settings and offer a scalable solution for diabetes prevention. The findings could also inform future interventions and policies aimed at curbing the rising burden of diabetes in low- and middle-income countries.

**Trial registration:**

CTRI/2022/02/040650 (registration date: 28.02.2022).

https://ctri.nic.in/Clinicaltrials/pmaindet2.php?EncHid=NjE2NzE=&Enc=&userName=

**Supplementary Information:**

The online version contains supplementary material available at 10.1186/s12889-025-24337-0

## Background

The rising prevalence of type 2 diabetes (T2D) and obesity represents significant public health challenges, necessitating urgent action for prevention and control. By 2045, the global prevalence of diabetes is projected to reach 700 million people [1], with cardiovascular disease (CVD) and diabetes currently contributing to 17.9 million and 1.5 million deaths annually, respectively. In India, the situation is particularly alarming, with 101 million individuals diagnosed with diabetes and 136 million with prediabetes [2].

Clinical trials have demonstrated that lifestyle interventions can prevent T2D, with benefits persisting years after the intervention ends [3, 4]. However, face-to-face programmes face challenges, including low acceptability due to time commitments, perceived stigma, and high costs, especially at scale [5]. Digital technologies offer a promising alternative, enabling personalized, lower cost and scalable interventions accessible to large populations. Digital delivery methods, such as mobile apps and text messaging, provide instant, interactive support for behaviour change, and can be tailored to individual needs.

Although most digital interventions have been studied in high-income countries [6–8], there is growing evidence of their effectiveness in low- and middle-income countries [9], including South Asia. For example, small scale studies with digital interventions in India have successfully demonstrated increased physical activity using a 100-day pedometer and an internet intervention [10]. Furthermore, a text messaging intervention with face-to-face lifestyle sessions has led to improved diet and reduced diabetes risk [11].

It is therefore timely to explore whether digital technologies can be leveraged to develop acceptable, effective, scalable and sustainable population health interventions for the prevention of T2D and CVD in South Asian men and women. In our pilot study conducted with 567 participants using a mobile app intervention, significant reductions in body weight were observed in both urban (−2.40 kg, 95% CI −3.10 to −1.69; *p* < 0.001) and rural populations (−1.19 kg, 95% CI −1.55 to −0.82; [*p* < 0.001]) [12]. The digital intervention components used in the pilot have been consolidated into a single, unified intervention for this current study.

This manuscript outlines the study protocol of the randomised controlled trial to assess the effectiveness of a digital intervention app (called My Sugar Journey) in T2D prevention compared to control (no digital intervention) among adults with prediabetes in urban and rural India.

## Methods/design

### Design

This is a cluster randomised, parallel group prospective study comparing the digital intervention group (Intervention group) and control group receiving usual care (Control group). (Fig. 1). A total of 3,240 participants will be recruited over 2 years from Delhi in the north (urban and rural) and Tamil Nadu (urban-Chennai and rural-Chunampet) in the south of India.

**Fig. 1 Fig1:**
[figure not shown]
Flow diagram of the diabetes prevention intervention study. A 2-step screening phase is incorporated prior to study recruitment and randomisation. Outcome of T2D incidence will be determined by the specific criterion applied to each individual on admission into the study (i.e. fasting glucose, 2-hour glucose on OGTT, and/or HbA1c). *****If haemoglobin < 10 g/L, inclusion criteria will be dependent on the fasting glucose or 2-hour post-OGTT glucose. Abbreviations: IDRS; Indian diabetes risk score; IFG, impaired fasting glucose; OGTT, oral glucose tolerance test

### Eligibility

#### Inclusion criteria

Participants eligible for the study must be adults aged 18 to 60 years old with an Indian Diabetes Risk Score (IDRS) of 30 or higher. IDRS is a simple, cost-effective tool developed to assess the risk of developing T2D in the Indian population and is widely used in community screening programs across India. The IDRS considers various risk factors relevant to the Indian population and assigns a score based on lifestyle, family history and anthropometric measures [13] Participants should have prediabetes, as defined by the WHO criteria [14], which includes impaired fasting glucose with levels between 110 and 125 mg/dL (6.1 to 6.9 mmol/L) and/or a 2-hour glucose level from an oral glucose tolerance test (OGTT) between 140 and 199 mg/dL (7.8 to 11.0 mmol/L) and/or an HbA1c of 6.0–6.4% (42–47 mmol/mol) based on the International Expert Committee (IEC) and National Institute for Health and Care Excellence (NICE) guidelines (rather than the definition by the American Diabetes Association (ADA)) to focus on individuals at the highest risk of conversion to diabetes [15, 16]. Participants must also be smartphone users with basic literacy skills in English, Tamil, or Hindi..

#### Exclusion criteria

Participants will be excluded from the study if they have pre-existing type 1 or type 2 diabetes, meet any criteria for type 2 diabetes (T2D) during screening, or are on oral hypoglycaemic agents or other medications that affect weight. Those who have undergone bariatric surgery, or plan to do so within the next 12 months, are also ineligible. Additionally, individuals who are pregnant, planning pregnancy, or unable to engage in physical activity as determined by their primary care provider, will not be included. Exclusion extends to those participating in other diabetes-related clinical trials, individuals with current or recent cancer (less than 12 months’ post-treatment), and anyone unable to participate due to other factors as assessed by the Chief Investigators.

### Sample size and feasibility

Based on our previous findings, the expected diabetes risk reduction based on previous face to face prevention studies has been shown to be 28–32%. We hypothesized that a digital intervention would enable a 24% reduction in the incidence of T2D (*p* < 0.05) compared to the control group. The effect size selected was based on published literature which suggests lower effectiveness for digital compared to face-face interventions.

To demonstrate that difference as significant at *p* < 0.05 and with 80% power and accounting for approximately 20% drop-out rate, 3,240 participants will be recruited.

### Ethics approval

The study has been given ethical approval for conduct in India by the Institutional Ethics Committee and registered with the Central Trials Registry of India (CTRI/2022/02/040650; registration date 28.02.2022). Each site also sought their own Institutional Ethics committee permissions from Devki Devi Foundation, New Delhi and Madras Diabetes Research Foundation, Chennai. Participant recruitment is currently ongoing.

### Participant screening

Participants will be identified through a targeted screening process conducted by the field team. During these visits, the research team will assess potential individuals based on the study’s preliminary inclusion criteria. Prior to participating in any study-specific screening activities, potential participants will be required to sign the approved informed consent form. Eligibility will be assessed through screening evaluations, and reasons for any exclusions will be recorded in a Participant Screening Log.

The study screening procedures are summarised in Fig. 1.

#### Screening STEP 1

During the first screening visit, eligibility will be evaluated based on the inclusion and exclusion criteria, the IDRS score, and random capillary blood glucose [13].

Participants meeting the criteria – defined as IDRS ≥ 30 and/or a random capillary blood glucose level ≥ 110 mg/dL – will proceed to the second stage of screening. In Asian Indians, a screening threshold of random capillary blood glucose ≥ 110 mg/dL is recommended [17].

#### Screening STEP 2

In this stage, a capillary oral glucose tolerance test (OGTT) [18, 19] will be performed and venous blood samples collected to measure HbA1c and haemoglobin levels. Additionally, anthropometric measurements, including blood pressure, height, weight, waist circumference, and body composition, will be recorded. Participants will also complete assessments related to quality of life (QOL-Eq. 5D), sleep patterns, alcohol use, smoking status, and socioeconomic status, the latter of which will be evaluated using a standardized scale relevant to India that considers occupation, income, and education – the Kuppuswamy Scale [20].

Participants meeting the inclusion criteria will be enrolled on to the study. For individuals with a haemoglobin less than 10 g/L, the HbA1c value will be disregarded, due to anaemia affecting glycated haemoglobin [21, 22]). In people with haemoglobin < 10 g/L, inclusion criteria will solely be dependent on the fasting glucose or 2-hour post-OGTT glucose. Participants diagnosed with T2D will be directed for specific diabetes care in local healthcare centres.

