### Primary and secondary outcomes

The primary outcome is incidence of T2D at 24 months (as determined by the specific criterion applied to each individual on their admission into the study (fasting glucose, 2-hour glucose on OGTT, and/or HbA1c). For example, if an individual’s prediabetes status was defined by HbA1c value (within the range 42-47mmol/mol), their progression to type 2 diabetes will be defined by the associated HbA1c threshold (48mmol/mol or greater). Changes over 6 and 12 months are considered secondary outcomes.

Secondary outcomes are listed in Table 1 and include changes in cardiometabolic outcomes; intervention uptake, use and satisfaction; behavioural and clinical outcomes; and costs related to implementation. Data will be collected at baseline, and 6, 12 and 24 months as outlined in Table 1.

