Another key factor in determining the success of the intervention is user adherence and engagement with the app. The study intervention offers a personalised approach to enhance individual engagement through gamification and motivation strategies, such as challenges, rewards, and progress tracking. By offering a more interactive experience, the app encourages sustained participation and adherence to healthy lifestyle changes, which are necessary for T2D prevention [23]. App data usage will be used to assess uptake with the digital intervention.

Finally, due to the high prevalence of anaemia in the South Asian population, which can affect HbA1c readings and lead to inaccurate assessments of diabetes risk [21, 22], recruitment is not based solely on HbA1c levels. This dual approach ensures more accurate identification of high-risk individuals. Another challenge in conducting studies in rural settings is the difficulty of using venous sampling and transporting blood samples to centralised laboratories, particularly due to limited infrastructure, logistical constraints and time taken. To address this, the study utilises capillary OGTT for more practical and immediate results in the field [28].

In conclusion, despite the challenges, the use of a digital platform reduces the need for extensive physical infrastructure and human resources, offering a scalable solution that could be highly cost-effective in resource-constrained environments. If proven successful, the study has the potential to contribute to the growing body of evidence supporting digital health solutions for diabetes prevention, with broader implications for public health policy and healthcare delivery in resource-constrained settings.

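### The haemoglobin cut-off for disregarding HbA1c is written as 10 g/L (1 g/dL), so as written the anaemia safeguard applies to effectively no one

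*Protocol article*

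**What the plan says.** The cut-off appears three times in the protocol article, always in g/L.

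- Participant screening, Screening STEP 2: "For individuals with a haemoglobin less than 10 g/L, the HbA1c value will be disregarded". The reason given there is that anaemia affects glycated haemoglobin.
- Same paragraph: "In people with haemoglobin < 10 g/L, inclusion criteria will solely be dependent on the fasting glucose or 2-hour post-OGTT glucose".
- Fig. 1 legend, in the note that carries the same number and unit: "inclusion criteria will be dependent on the fasting glucose or 2-hour post-OGTT glucose".

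The Discussion explains why the rule exists. Recruitment does not rest on HbA1c alone "due to the high prevalence of anaemia in the South Asian population, which can affect HbA1c readings".

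Three other sections determine what the rule controls. The inclusion criteria list HbA1c as one of several alternative routes to prediabetes: "and/or an HbA1c of 6.0–6.4% (42–47 mmol/mol" and so on. The exclusion criteria remove a person who satisfies any one of the T2D criteria at screening. Under Primary and secondary outcomes, the entry criterion also fixes the endpoint. For someone admitted on HbA1c, "their progression to type 2 diabetes will be defined by the associated HbA1c threshold (48mmol/mol or greater".

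**The concern.** A haemoglobin of 10 g/L is far below anything expected in an adult who walks into a community screening visit. A rule meant for a condition that the article itself calls common has therefore been given a threshold that nobody would meet. No other haemoglobin value in the article corrects it.

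The threshold is a decision rule for eligibility, and it also reaches the primary outcome. If HbA1c is kept when it should have been set aside, a person can be enrolled, or turned away, on a reading the article regards as unreliable. Someone enrolled that way then has incident T2D at 24 months judged on the same measure. The Ethics approval section says recruitment is under way, so the question of which value is in use is a live one.

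**Working it through.** **Inputs.** The cut-off is haemoglobin < 10 g/L (Screening STEP 2, twice; Fig. 1 legend, once). Planned enrolment is 3,240. HbA1c is 42–47 mmol/mol for prediabetes (Inclusion criteria) and 48 mmol/mol or more for T2D (Primary and secondary outcomes).

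**Unit conversion.** 1 L = 10 dL, so 10 g/L ÷ 10 = 1 g/dL. The same numeral in g/dL would be ten times higher, which is why a unit slip is the likely explanation.

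**Share covered as written.** This takes as an assumption, from general knowledge and not from the article, that no ambulatory screenee has haemoglobin below 1 g/dL. The rule then covers effectively 0 of 3,240 participants, and effectively nobody screened.

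**Who would be affected if the literal value were applied.** Take a person whose haemoglobin is below the intended cut-off, whatever that is. Everyone reaching STEP 2 has both an OGTT and an HbA1c. Here glucose means the fasting and 2-hour values together. I read the instruction to disregard HbA1c as covering exclusion as well as inclusion.

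| Glucose | HbA1c (mmol/mol) | HbA1c disregarded | HbA1c kept | What changes |
|---|---|---|---|---|
| Below prediabetes | under 42 | not enrolled | not enrolled | nothing |
| Below prediabetes | 42–47 | not enrolled | enrolled on HbA1c | eligibility, and the outcome rests on HbA1c |
| Below prediabetes | 48 or more | not enrolled | excluded as T2D | not enrolment |
| Prediabetes | under 42 | enrolled on glucose | enrolled on glucose | nothing |
| Prediabetes | 42–47 | enrolled on glucose | enrolled on both | outcome criterion may become, or include, HbA1c |
| Prediabetes | 48 or more | enrolled on glucose | excluded as T2D | eligibility |
| Diabetes | any of the three | excluded | excluded | nothing |

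The last row stands for three combinations, so there are nine in all. Enrolment changes in two of them, and the outcome criterion alone may change in a third. In the other six, neither enrolment nor the outcome criterion changes.

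**Size.** The number of people in those three combinations depends on the intended cut-off, the prevalence of anaemia below it, and the joint distribution of glucose and HbA1c. The article gives none of these, so no count or percentage can be derived.

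**The case against.** The strongest reply is that this is an obvious unit slip in a condensed article. The purpose of the rule is spelled out, and staff looking at real haemoglobin values would see at once that the printed threshold cannot be meant. Every person at STEP 2 also has an OGTT, and the Discussion says recruitment does not depend on HbA1c alone. Both arms follow the same rule, so nothing suggests that any misclassification would differ by arm.

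Much of that stands. A slip is the likely explanation. A reader might infer from the three appearances that the error must be more than a slip, but two of them sit in the same paragraph and the third is a legend in nearly the same words. One unit error carried through would produce all three. Repetition does argue against a text-extraction fault, but it says nothing about practice at the sites. A reader might also infer that everyone below the intended cut-off is misrouted. The table shows otherwise: many such people are enrolled or excluded identically either way.

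Two parts of the reply do not stand. Doing an OGTT on everyone does not stop a person qualifying on HbA1c alone, because the criteria are alternatives. And the fact that a threshold is recognisably wrong does not show which value is in use. The article offers no correct figure to fall back on.

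**Conclusion.** The threshold is wrong as written. It covers effectively no participant and contradicts the purpose given for it in Screening STEP 2 and the Discussion. That conclusion rests on the unit conversion and on the assumption that haemoglobin below 1 g/dL is not seen in ambulatory screenees.

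Any consequence for the trial is conditional on sites applying the printed value. In that case it falls on the subset for whom HbA1c alone decides eligibility (HbA1c in the prediabetes range with non-qualifying glucose, or in the diabetes range with prediabetic glucose), and on those whose 24-month criterion becomes HbA1c because it was not set aside. The size of that subset is unknown.

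It would be tempting to conclude that anaemic people are now being admitted on unreliable HbA1c, or that the primary comparison is biased. The article supports neither: it does not show the operational rule, and it gives no basis for a difference between arms.

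**What to change.** - The sponsor confirms the intended haemoglobin value and unit. No replacement is proposed here.
- Correct all three statements (two in Screening STEP 2, one in the Fig. 1 legend), and reconcile them with the full protocol and with the eligibility rule that the sites actually use.
- If the sites used the intended value throughout, a published correction is enough.
- If the literal value was used in the field, check participants who entered on HbA1c, alone or with glucose, against the confirmed cut-off. Flag those below it, and report a sensitivity analysis of the primary outcome that addresses them. People wrongly excluded cannot be recovered this way, but the Participant Screening Log could be used to count them, so far as it can be linked to their STEP 2 results.

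The cost is small. The correction is a matter of text, and haemoglobin is already collected at STEP 2, so the conditional check is a database query and one additional analysis, with no new measurements.

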### Participant recruitment and cluster randomisation

Participants will be cluster randomised from both urban and rural areas across Tamil Nadu and Delhi (Fig. 2). Using STATA software, clusters will be randomly allocated in a 1:1 ratio to either the control group, which will receive the standard of care, or the intervention group, which will receive the digital intervention.

**Fig. 2 Fig2:**
[figure not shown]
Summary of participant and cluster recruitment in urban and rural Chennai and Delhi. A total of 60 clusters (30 urban and 30 rural) will be recruited in Chennai, with 30 clusters (15 urban and 15 rural) in Delhi. Each cluster represents 36 participants to be recruited

In Tamil Nadu, a total of 60 clusters (30 urban and 30 rural) will be established to recruit 2,160 participants (Fig. 2). The Chennai city (urban) has 200 wards, with 68 wards having a population density greater than 10,000. Each urban ward will constitute a single cluster, with 36 participants recruited per cluster. In rural areas, three villages will be grouped together to form one cluster to achieve the target of 36 participants per cluster. This approach accounts for the anticipated lower prevalence of prediabetes in rural areas compared to urban settings, requiring more extensive screening to meet the cluster size.

Similarly, in Delhi, a total of 30 clusters (15 urban and 15 rural) will be recruited. Delhi’s urban population is organized into blocks, while the rural population is divided into clusters. The study will screen 15 urban clusters (2 or 3 blocks will be combined to form a cluster) with a population density of 29,638 and 15 rural clusters with a population density of 29,434. Both in urban and rural areas, participants will be screened till the target of 36 participants per cluster is achieved.

### Study intervention

A description of activities at each visit has been outlined below and a summary provided in Table 1.

**Table 1 Tab1:** Quantitative outcome measures

Outcome measures	Baseline	Month 6	Month 12	Month 24
Demographics	X			
Anthropometrics (height, body weight, waist circumference, BMI)	X	X	X	X
HbA1c	X		X	X
Capillary oral glucose tolerance test	X		X	X
Systolic and diastolic blood pressure	X	X	X	X
Food frequency questionnaire	X	X	X	X
Physical activity – MPAQ questionnaire	X	X	X	X
Lifestyle questionnaire - smoking, alcohol	X	X	X	X
Socioeconomic status tool	X			X
App engagement and usage outcomes^a^				
Total time spent per participant on app per day/week/month/entire duration	X	X		
App session interval (i.e. time between visits to the app)	X	X		
Number of sessions per participant on app per day/week/month/entire duration	X	X		
MARS questionnaire (for intervention group only)		X		
Economic outcomes				
QOL-EQ -5D	X	X	X	X
Collection of hospital care and associated costs	X	X	X	X

^a^For intervention group only

Abbreviations: *BMI*, body mass index; *HbA1c*, glycated haemoglobin; *MARS*, mobile application rating scale; *MPAQ*, Madras diabetes research Foundation - Physical activity questionnaire; *QOL-EQ-5D*, quality of life EuroQol Group-5D questionnaire

After randomization, study participants will receive instructions on how to proceed in the study according to their study group. Individuals in the control group will receive an educational session, either via telephone or will be directed to a local healthcare clinic. Standard educational materials will be provided on lifestyle risk factors of T2D and recommendations on a healthy diet and physical activity in accordance with international and national recommendations.

For participants assigned to the digital intervention group, the research team will conduct home visits to administer study questionnaires, assist with downloading the digital intervention app, and complete the onboarding process. During this visit, participants will receive a brief overview of the app’s functionality and features.

After the 6-month intervention period, participants will continue to have access to the digital app on their phones and may use it at their discretion. However, no further active engagement will be provided, such as notifications, nudges, or telephone calls. Participants are free to interact with the app’s features as they wish.

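### The article places app-arm questionnaires after allocation, at the visit that installs the app, and gives no other place for baseline diet, activity and cost data

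*Protocol article*

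**What the plan says.** Four parts of the protocol article bear on this.

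- **Order of events.** The legend to Fig. 1 says: "A 2-step screening phase is incorporated prior to study recruitment and randomisation". Both screening steps therefore come before allocation.
- **Screening Step 2.** Besides the glucose tests, blood samples and body measurements: "Participants will also complete assessments related to quality of life (QOL-Eq. 5D), sleep patterns, alcohol use, smoking status, and socioeconomic status". Diet, physical activity and hospital-care costs are not named.
- **Study intervention.** The arm-specific text opens with "After randomization, study participants will receive instructions on how to proceed in the study according to their study group". For controls: "Individuals in the control group will receive an educational session, either via telephone or will be directed to a local healthcare clinic", with standard educational materials. For the app arm: "For participants assigned to the digital intervention group, the research team will conduct home visits to administer study questionnaires, assist with downloading the digital intervention", with onboarding completed at the same visit.
- **Table 1 and Primary and secondary outcomes.** The rows "Food frequency questionnaire" and "Physical activity – MPAQ questionnaire", and the row for hospital care and its costs, are marked at baseline and months 6, 12 and 24. Only the app-engagement rows and the app rating scale are restricted to the intervention group. On their role: "Secondary outcomes are listed in Table 1 and include changes in cardiometabolic outcomes; intervention uptake, use and satisfaction; behavioural and clinical outcomes".

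**The concern.** A baseline supports a randomised comparison of change when it is measured before participants know their arm, and in the same way in both arms. Here the only questionnaire administration described outside screening takes place after assignment, in the app arm, at the visit that sets up the app.

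The app's stated goals include better diet and more physical activity, which are what the food frequency questionnaire and the MPAQ measure by self-report. Someone who has just been assigned a lifestyle app, and is answering the team that installs it, may report differently from someone who does not yet know the arm. The direction is not predictable. A flattering baseline would hide real improvement, and an unflattering one would create apparent improvement.

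At stake are the self-reported diet and activity outcomes and, to a lesser degree, the cost items. The primary outcome rests on glucose and HbA1c and is not touched.

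**Working it through.** **Step 1: where can each baseline questionnaire be collected?**

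| Table 1 baseline item | Named at Step 2 (before randomisation)? | Other place in the article |
|---|---|---|
| Quality of life (EQ-5D) | yes | not needed |
| Smoking, alcohol | yes | not needed |
| Socioeconomic status | yes | not needed |
| Food frequency questionnaire | no | app-arm home visit only, unnamed |
| MPAQ | no | app-arm home visit only, unnamed |
| Hospital care and costs | no | app-arm home visit only, unnamed |

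The problem is confined to the last three rows. For controls the article gives no place for them, although Table 1 requires them.

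**Step 2: what would a baseline shift do?** The article states no figure to reproduce here, so this is an illustration.

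Inputs from the article: 3,240 participants (90 clusters of 36), 1:1 allocation, about 20% drop-out.
- Per arm: 3,240 × 0.8 / 2 = 1,296.
- Mean evaluable cluster size: 36 × 0.8 = 28.8.

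Assumptions not in the article: ICC of 0, 0.02 or 0.05; no true effect; a shift of 0.05 or 0.10 SD in the app arm's baseline report only; SD of change equal to the SD of the measure. With equal SDs at the two times, the last assumption implies a baseline–follow-up correlation r of 0.5, because the variance of change is 2(1 − r) = 1.

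*Unadjusted change scores*
- Design effect DE = 1 + (28.8 − 1) × ICC = 1.000, 1.556, 2.390.
- SE of the arm difference = √(2 × DE / 1,296) = 0.039, 0.049, 0.061 SD.
- False-positive rate = P(|Z + shift/SE| > 1.96). At ICC 0.02 and 0.10 SD, shift/SE = 0.10 / 0.0490 = 2.04, giving 0.53.

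*Baseline-adjusted analysis with r = 0.5*
- Bias = r × shift, so 0.10 SD becomes 0.05 SD.
- SE is multiplied by √(1 − 0.25) = 0.866, giving 0.034, 0.042, 0.053.
- At ICC 0.02 and 0.10 SD, bias/SE = 0.05 / 0.0424 = 1.18, giving 0.22.

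| Assumed shift | Analysis | ICC 0 | ICC 0.02 | ICC 0.05 |
|---|---|---|---|---|
| 0.10 SD | change score | 72% | 53% | 38% |
| 0.10 SD | baseline-adjusted | 31% | 22% | 16% |
| 0.05 SD | change score | 25% | 18% | 13% |
| 0.05 SD | baseline-adjusted | 11% | 9% | 8% |

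The nominal rate is 5%. Adjustment reduces the problem considerably but does not remove it.

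**The case against.** The strongest reply is that much of this is read from silence. The article does not say that controls receive no questionnaire visit. Table 1 and the outcomes section schedule the same baseline for everyone, and a condensed article may leave control-arm logistics to the full protocol. The home-visit questionnaires are neither named nor called baseline. The Step 2 list is not presented as complete: demographics, also a baseline item, is missing from it too.

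Most of this stands, and it limits the point. A reader might infer that the home visit is made only to the app arm, that the two arms' baselines therefore differ in timing, setting and knowledge of arm, or that controls have no diet and activity baseline at all. The documents support none of these. A difference in knowledge of arm would require controls to answer before allocation is known, which is not stated. A missing control baseline would contradict Table 1. Nor is it true that study questionnaires in general come after allocation: quality of life, sleep, alcohol, smoking and socioeconomic status are taken at Step 2 from everyone.

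The reply does not remove what the article does state: app-arm questionnaires are given after assignment, at the onboarding visit. That is a described procedure rather than a missing detail. If controls are also questioned after allocation, both arms would give these baselines knowing their arm, and the same correction would apply.

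The false-positive rates can fairly be challenged too. The shift is assumed, and the change-score rows are the less favourable analysis. They show sensitivity at this sample size and do not predict what will happen.

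**Conclusion.** The point holds in a limited form. The text puts app-arm questionnaire administration after allocation, at the visit that installs the app, and offers no other place for the baseline food frequency questionnaire, MPAQ and cost items. That those instruments are the ones given at the visit is reached by elimination. The placement after allocation is certain from the text; an actual difference between the arms' baselines is possible but not established.

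The size depends on an unknown reporting shift. For 0.10 SD at ICC 0.02, the false-positive rate would be about 53% with unadjusted change scores and about 22% with baseline adjustment at correlation 0.5. For 0.05 SD the corresponding rates are about 18% and 9%. The reach is limited to self-reported diet, activity and cost secondary outcomes. It should be corrected, because recruitment is described as ongoing and the correction is cheap.

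**What to change.** - State that the baseline food frequency questionnaire, MPAQ and cost items are completed in both arms, by the same mode, before the cluster's allocation is disclosed. This can be at Screening Step 2 or once eligibility is confirmed. EQ-5D, smoking, alcohol and socioeconomic status are already at Step 2 and need no move.
- Limit the post-allocation home visit to app download and onboarding, and make the Study intervention text, the Step 2 list and Table 1 agree.
- For participants already enrolled whose diet and activity questionnaires were completed after allocation, compare follow-up values between arms without using those questionnaires as the baseline.

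**Cost.** The pre-allocation contact becomes longer and the home visit shorter. If the questionnaires are done during the OGTT wait, some people later found ineligible will complete them too, since eligibility depends on results not yet available; waiting until eligibility is confirmed avoids that. Where the baseline is dropped, under r = 0.5 the follow-up comparison has the same SE as a change score, and an SE about 15% larger than a baseline-adjusted analysis (1 / 0.866 = 1.155). The change does not address self-report at months 6, 12 and 24, when participants will know their arm in any case.
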